## Abstract

**Background:**

Skin grafting is currently the gold standard for managing traumatic skin defects. However, split-thickness skin grafting, the most common technique, is challenging because it yields a limited amount of skin and creates a new wound at the healthy donor site. RECELL (Avita Medical), a noncultured skin cell suspension technique, yields healing outcomes with comparable duration and quality to skin grafting for burn trauma. Although RECELL is widely used for burn trauma, its use for severe traumatic skin defects is not yet prevalent in Japan.

**Objective:**

This study aims to evaluate the utility of the RECELL skin reconstruction technique in trauma cases involving significant skin defects. Specifically, the primary aim is to validate the efficacy of the RECELL skin reconstruction technique when combined with split-thickness mesh grafting in patients with significant posttraumatic skin defects, with a particular focus on wound closure and scar quality.

**Methods:**

This prospective, single-center, open-label pilot study will enroll patients aged 16 years and older with traumatic limb skin defects ≥160 cm² and sufficient dermal-like tissue. Participants will undergo RECELL-assisted autologous skin grafting with mesh grafts under general anesthesia. Wound healing, scarring (Vancouver Scar Scale), and pain (visual analog scale) will be assessed up to 24 weeks postoperatively. The primary end point is ≥95% reepithelialization at postoperative day 14. Descriptive statistical analyses will be performed to evaluate outcomes and inform future randomized trials.

**Results:**

Patient recruitment began in April 2024 and is currently ongoing in our hospital. As of April 10, 2025, 10 patients had been screened, of whom 4 were enrolled. No adverse events or protocol deviations have been noted.

**Conclusions:**

This study aims to validate the utility of RECELL for skin defects resulting from trauma by assessing wound closure and scar formation, including adverse events, delayed healing, infection, and durability.

## Introduction

Skin grafting is currently the gold standard for managing skin defects [1]. Split-thickness skin grafting, the most common technique, is challenging because it yields a limited amount of skin and creates a new wound at a healthy donor site [2]. For extensive skin defects caused by severe trauma, such as open fractures or degloving injuries, the limited availability of harvested skin often necessitates extended coverage using mesh grafting. However, epithelialization of the meshed area requires a considerable amount of time, and the cosmetic outcome may be less than ideal [3-6]. RECELL (Avita Medical) is a regenerative technique that uses the skin cells of a patient to create a noncultured skin cell suspension for wound healing [7-9]. This suspension is applied to the wound, enabling closure without extensive skin grafting. Although RECELL is widely used for burn trauma, its use for severe traumatic skin defects is not yet prevalent in Japan. To our knowledge, only a few studies have investigated the use of RECELL in patients with extremity trauma [10]. Therefore, this study aimed to evaluate the efficacy of the RECELL skin reconstruction technique in patients with significant posttraumatic skin defects.

While numerous preceding studies have demonstrated the utility of RECELL in the treatment of burn wounds, there are critical differences between burn and traumatic wounds. Burn wounds are typically clean and are primarily characterized by thermally induced vascular damage. In contrast, traumatic wounds, particularly those resulting from crush or degloving injuries, carry a higher risk of contamination and often involve deeper and more complex tissue damage, including damage to blood vessels and subcutaneous structures. However, in large traumatic defects, if a clean and well-vascularized wound bed can be successfully prepared, there is a potential to achieve a higher graft take rate compared to burns, as the peripheral microcirculation may be relatively preserved. Currently, robust data demonstrating the efficacy of RECELL in combination therapy for large traumatic skin defects are lacking. To address this knowledge gap, we sought to clarify the treatment outcomes of layered skin grafting incorporating the RECELL system for traumatic soft tissue defects. Currently, RECELL is not covered by Japanese insurance for the treatment of traumatic skin defects. The findings of this study will aid in the expansion of RECELL technology application in trauma cases. Therefore, the primary aim of this study is to assess the utility and safety of RECELL combined with split-thickness meshed skin grafting in the reconstruction of large posttraumatic skin defects.

## Methods

### Study Design, Participants, and Setting

This is a single-center, open-label, uncontrolled, single-arm, comparative prospective study.

The participants will be patients with open limb wounds transported to our center by ambulance for treatment, with good subcutaneous granulation tissue formation. Furthermore, considering that the area of the skin defect covered by one RECELL 1 kit is 160 cm^2^, we targeted patients with epidermal defects measuring ≥160 cm^2^. Given that the number of such cases transported to our hospital in the past was approximately 5 per year, we decided to target cases over a period of 2 years. The study period will therefore last from April 1, 2024, to March 31, 2026.

### Ethical Considerations

This study will be conducted in compliance with the Declaration of Helsinki and the Clinical Trial Act of the Ministry of Health, Labour, and Welfare in Japan. The investigators will provide each participant with a sufficient explanation of the study and obtain written informed consent to participate. The study protocol has already been approved by the Nara Medical University Certified Review Board (CRB5200002). The trial has been registered on the Japan Registry of Clinical Trials (jRCTs052230203). This study followed the SPIRIT (Standard Protocol Items: Recommendations for Interventional Trials) guidelines (Checklist 1). All study data will be handled confidentially and stored securely. Participants have the right to withdraw consent at any time without penalty, and their participation data will be handled according to the ethical approval guidelines. All adverse events and serious adverse events will be recorded, investigated, and promptly reported to the Nara Medical University Certified Review Board as required by the protocol. This study will be conducted as part of regular treatment and will not involve any compensation to the participants.

### Inclusion and Exclusion Criteria

This study will include patients with skin defects due to trauma (excluding burns caused by flames, excessive heat, or skin exposure to steam or hot water) or skin defects due to skin flaps. Eligible patients must have a skin defect area of ≥160 cm², excluding the hands and face, and sufficient dermal-like tissue formed at the test site. Participants must be aged 16 years or older at the time of consent and provide written informed consent. For those younger than 18 years, written consent will be obtained from their parents or legal guardians. The area to be grafted will be defined as an area considered difficult to treat with standard skin grafting, based on the range of indications for burns in Japan.

The study will exclude patients younger than 16 years; those with hypersensitivity to sodium lactate (washing solution), anesthetics, adrenaline, povidone-iodine, or chlorhexidine; and those with allergies to ingredients derived from pigs. Furthermore, patients will be excluded if they are judged to be unsuitable for study by the principal investigator (or subinvestigator). The face was defined as an excluded affected region due to cosmetic and anatomical complexity that requires specialized reconstructive techniques beyond the scope of this protocol. The selected size of ≥160 cm^2^ was chosen not only because it is the effective coverage area of one standard RECELL kit but also to address the efficacy gap identified in the literature regarding large posttraumatic defects. The exclusion criteria were chosen because, although this study considered skin loss due to trauma, treating limb injuries with skin grafts on the hands is highly likely to lead to significant functional impairment and is therefore generally not recommended. Furthermore, allergic reactions to the medications used were considered a contraindication, and therefore patients who exhibit such reactions will be excluded.

### Surgical Treatment Protocol

The enrolled patients will undergo surgery according to the study protocol. Under general anesthesia, skin grafts will be harvested from healthy skin donor sites (the groin, thigh, or scalp). In addition to the RECELL skin grafts, the necessary amount of mesh skin grafts will be collected. A mesh graft will be applied to the defect site where it is to be placed, and a noncultured cell suspension, previously prepared using RECELL, will be sprayed onto the mesh-grafted area. A nonadherent gauze will be applied to the skin graft, and the gauze will be placed over it for bandage fixation.

### Postsurgical Treatment

The bandaged treatment site will be uncovered 6 to 8 days postoperatively, and the wounds will be evaluated at 24 weeks postoperatively. The administration of antibiotics, anticoagulants, steroid ointments, and any type of dressing material will be permitted. However, the following combined treatments will not be allowed: full-layer skin grafts, negative pressure wound closure therapy used solely for skin graft fixation, and cytotoxic drugs (eg, sulfadiazine silver–containing preparations).

Treatment after completing the protocol may include washing, ointment therapy, and negative pressure wound closure therapy. Treatment will be administered at the discretion of the principal investigator and research associate.

### Study Data Collection

This study will involve a comprehensive collection of the participants’ data. This will be initiated by recording the participants’ background information, including age, sex, height, weight, blood pressure, pulse rate, and body temperature, along with a detailed survey of their current and previous medical histories, as well as any underlying medical conditions present at the time of inclusion in the study.

Subsequently, a series of blood tests, including white blood cell, red blood cell, hemoglobin, hematocrit, and platelet counts, along with coagulation indicators, such as the prothrombin time-international normalized ratio and activated partial thromboplastin time, will be performed. We will also measure the levels of fibrinogen, fibrin degradation products, and a range of biochemical markers, including aspartate aminotransferase and alanine aminotransferase, lactate dehydrogenase, creatine phosphokinase, blood urea nitrogen and creatinine, and C-reactive protein.

For the trauma data, the cause and mechanism of injury will be documented in detail. During the protocol surgery, we will evaluate the recipient site by measuring its long and short diameters and thickness and noting any previous treatments and the method of excision. We will record the magnification of the mesh skin graft and the dimensions of the skin donor site. Photographic records of the recipient sites will be obtained immediately before and after surgery.

Posttreatment follow-up will be performed at 1, 2, 4, 6, 8, 12, and 24 weeks. The tolerance levels applied to the follow-up examination dates are defined in Table 1. During the posttreatment follow-up, we will carefully observe the healing of the recipient site; assess scarring using the Vancouver Scar Scale (VSS) [11]; survey patient satisfaction with the treatment; and observe delayed healing, infections, or scarring requiring surgical intervention. For these evaluations, particularly the photographic records and VSS assessments, the same evaluator will assess each patient whenever possible.

**Table 1. T1:** Schedule of follow-up visits and tolerance levels.

Time point		Tolerance level
**Pretreatment**		
−7 days up to treatment		—^a^
**Day 0**		
Treatment day		—
**Posttreatment**		
After 1 week		±1 day
After 2 weeks		±3 days
After 4 weeks		±5 days
After 6 weeks		±6 days
After 8 weeks		±7 days
After 12 weeks		±10 days
After 24 weeks		±14 days

a Not available.

Finally, pain and concomitant treatments will be evaluated. Pain at both the recipient and donor sites will be evaluated using a visual analog scale (VAS). We also plan to maintain a detailed record of any concurrent treatments, including the names, daily doses, and durations of antibiotics and anticoagulants, as well as the types of dressing materials and steroid ointments used. A CONSORT (Consolidated Standards of Reporting Trials)–style timeline of the planned patient enrollment and assessment is shown in Table 2.

**Table 2. T2:** Timeline of the preoperative and postoperative assessment protocol for this study.

	Pretreatment	Treatment day	After 1 week	After 2 weeks	After 4 weeks	After 6 weeks	After 8 weeks	After 12 weeks	After 24 weeks
Obtaining consent	✓								
Photography: test site		✓	✓	✓	✓	✓	✓	✓	✓
Healing of the test site			✓	✓	✓	✓	✓	✓	✓
Scar assessment (VSS^a^)								✓	✓
Subject satisfaction after treatment								✓	✓
Delayed healing of test site					✓	✓	✓	✓	✓
Presence of wound infection		✓	✓	✓	✓	✓	✓	✓	✓
Scars requiring surgical intervention			✓	✓	✓	✓	✓	✓	✓
Assessment of pain at the test site (VAS^b^)			✓	✓	✓	✓	✓		
Diseases failure			✓	✓	✓	✓	✓		
Concomitant treatment survey			✓	✓	✓	✓	✓	✓	✓

a VSS: Vancouver Scar Scale.

b VAS: visual analog scale.

Five years after the end of the study, the information will be processed so that specific individuals cannot be identified unless the information is matched with other information, and the records will be supplemented.

### Data Analysis

This study is designed as a prospective, single-arm pilot study. Given the lack of robust data on RECELL for large traumatic defects, a formal power calculation is not feasible for the primary end point. Therefore, we aim to enroll 10 patients over 2 years, which will provide the descriptive data necessary to inform the design and power calculation for a subsequent randomized controlled trial.

The primary end point is the achievement of ≥95% reepithelialization at the recipient site, assessed at postoperative day 14 (±3 days tolerance), corresponding to the final planned dressing change within the early healing phase (refer to Table 2). We determined that 14 days was appropriate based on our past case experience and several published studies [12-14]. The secondary end points, including the VSS and VAS for scar assessment, will be primarily evaluated at the final observation point of 24 weeks postoperatively (and also at 12 weeks), as detailed in Table 2.

Descriptive analyses for continuous variables will be presented as the mean and SD. Categorical variables will be presented as counts and percentages. Any missing data will be reported, and the analysis will use a complete case analysis approach, given the pilot nature and short follow-up period. Although this is a single-arm pilot study, exploratory comparisons of the primary outcome (reepithelialization rate) and VSS scores will be made against published historical controls to inform the sample size calculation for future randomized controlled trials. Descriptive analyses, including central tendency (mean and median) and variability, will be performed after data collection is completed.

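### The VAS is to be evaluated at weeks 24 and 12, but Table 2 schedules test-site VAS only at weeks 1 to 8

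*Protocol article*

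**What the plan says.** **Analysis time points (Protocol article, Data Analysis).** The secondary end points, "including the VSS and VAS for scar assessment, will be primarily evaluated at the final observation point of 24 weeks postoperatively", are also to be looked at once earlier: "and also at 12 weeks), as detailed in Table 2". The sentence therefore names two visits for the VAS, weeks 24 and 12, and sends the reader to Table 2 for the detail.

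**Collection schedule (Study Data Collection, Table 2).** The row "Assessment of pain at the test site (VAS^b" is ticked at weeks 1, 2, 4, 6 and 8, and its cells for weeks 12 and 24 are empty. The row "Scar assessment (VSS^a" is ticked at weeks 12 and 24 only.

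**What the VAS measures.** The text before Table 2 states: "Pain at both the recipient and donor sites will be evaluated using a visual analog scale (VAS". The Methods paragraph of the abstract also treats it as a pain scale, in a sentence covering wound healing, scarring and pain that ends: "pain (visual analog scale) will be assessed up to 24 weeks postoperatively". Only Data Analysis links the VAS to scars.

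**The concern.** The analysis sentence and the table it cites disagree about when the VAS exists. Anyone running the study from Table 2 will not record it at weeks 12 or 24. Anyone analysing the study from Data Analysis will look for it at exactly those visits. Because the plan specifies complete case analysis, a VAS summary at either time point would have no cases.

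What is at stake is one named secondary end point. The study aims at 10 patients and is meant to supply descriptive data for a later randomized trial. Recruitment is already under way, and a pain score not taken at a visit cannot be recovered later. If the conflict stays until the data are in, someone must then decide which of five earlier visits stands for the VAS, in an open-label study and with no rule fixed beforehand.

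**Working it through.** The article gives no figure to reproduce here. The check sets the schedule against the analysis sentence, and then asks whether the visit windows could reconcile them.

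**Step 1. Is the table read correctly?** The header of Table 2 has a label cell and nine time-point columns (10 cells). The VAS, VSS and healing rows also have 10 cells each, so no tick has shifted between columns. The healing row is ticked at all seven follow-up visits, so the week-12 and week-24 columns are in use.

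**Step 2. Planned collection against planned analysis.**

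| Measure | Visits ticked in Table 2 | Visits named in Data Analysis | In common |
|---|---|---|---|
| VSS | 12, 24 | 24, 12 | 12, 24 |
| VAS (test site) | 1, 2, 4, 6, 8 | 24, 12 | none |

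The sentence fits the VSS exactly. For the VAS, 0 of the 2 named visits are scheduled.

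**Step 3. Could a late week-8 visit count as week 12 or week 24?** Table 1 gives "After 8 weeks ±7 days" and "After 12 weeks ±10 days", and a tolerance of 14 days either side at week 24. The window is 7 × week ± tolerance:

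- Week 8: 56 ± 7, days 49 to 63
- Week 12: 84 ± 10, days 74 to 94
- Week 24: 168 ± 14, days 154 to 182

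The latest in-window week-8 value (day 63) comes 74 − 63 = 11 days before the week-12 window opens and 154 − 63 = 91 days before the week-24 window opens. The tolerances do not close the gap.

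**Step 4. Could Data Analysis mean a separate scar VAS?** No such scale is described in Study Data Collection. The only scar-scale row in Table 2 is the VSS, and the only VAS row is pain. Under that reading too, nothing is scheduled at weeks 12 or 24.

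**Step 5. What else depends on the VAS?** The planned comparisons with published historical controls cover reepithelialization and VSS scores, not the VAS. The primary end point is read at day 14 (± 3 days).

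**The case against.** The best defence is that the sentence describes the secondary end points as a group, says only that they are mainly evaluated late, and defers to Table 2. Table 2 would then govern, and the VAS would simply be an early pain measure. That may well be the intention. But the sentence names the VAS explicitly, and if Table 2 governs, five visits remain with none singled out. The conflict still needs an edit.

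Other objections limit the point, and they stand:

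- **Weight.** This is an uncontrolled descriptive pilot with no formal test planned for the VAS, and the VAS is not among the historical comparisons.
- **Loss of pain data.** A reader might infer that pain data are missing altogether. They are not: five post-treatment assessments are scheduled. Only the values at the two named analysis visits are absent, and only if Table 2 is the passage that is followed.
- **The abstract.** A reader might take it as promising pain scores at week 24. Its sentence covers healing, scarring and pain together, so the 24 weeks can be the follow-up limit for the whole set. It adds to the ambiguity but does not settle which passage is wrong.
- **Donor-site pain.** A reader might infer from the test-site label that donor-site VAS is scheduled at no visit. Table 2 is not exhaustive: it has no row for the vital signs, blood tests or injury data that Study Data Collection requires. A missing row in an abridged table does not prove that the assessment is unscheduled. This does not rescue the test-site VAS, whose row is present with the two cells blank.
- **Choice of visit after the fact.** Nothing in the article suggests that the investigators plan this. The unreconciled text merely leaves room for it.

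**Conclusion.** The inconsistency is real and follows from the article's own wording. Data Analysis fixes the VAS at weeks 24 and 12, Table 2 collects it at weeks 1, 2, 4, 6 and 8, and the two sets have no visit in common. If Table 2 is followed, the VAS end point has no scheduled observation at either stated time point. That conclusion assumes that Table 2 reflects the schedule in use. The article does not show whether the table or the sentence is the mistake, so the two must be reconciled.

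The size is modest: one secondary end point, reported descriptively. The primary end point, the VSS and the historical comparisons are untouched. It should be fixed, but it is not a defect on which the study stands or falls. The link between the VAS and scar assessment is a labelling slip in the same sentence. The donor-site question is a matter of clarity only.

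**What to change.** Reconcile Data Analysis, Table 2 and the abstract in one of two ways.

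1. **Keep the late time points.** Tick the VAS at weeks 12 and 24 in Table 2. Both visits already take place, so no visit is added. Report the value as not collected for any patient already past them. The article reports 4 patients enrolled by April 10, 2025 but no treatment dates, so anywhere from 0 to 4 of them could have been affected at that date.
2. **Keep the early schedule.** Change Data Analysis to name, in advance, one VAS time point among weeks 1, 2, 4, 6 and 8, and list the other visits as supportive. This creates no gap for patients already treated. The abstract should then say that pain is followed to week 8.

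Under either option, describe the VAS in Data Analysis as a pain end point. For clarity, state in Table 2 whether the VAS row also covers the donor site, which the accompanying text requires.

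The cost is an edit to one table row and one sentence, with a matching line in the abstract if option 2 is taken. Option 1 also adds one short rating at each of two existing visits. Because recruitment is in progress, the choice should be made and dated before the VAS data are summarized.

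### Complete-case analysis of the day-14 closure end point can inflate the rate when a failed graft leaves no day-14 value

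*Protocol article*

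**What the plan says.** The Data Analysis section defines the outcome: "The primary end point is the achievement of ≥95% reepithelialization at the recipient site", assessed at day 14 with a 3-day tolerance either side. The same section fixes how gaps are handled. It promises to report missing values and adds that "the analysis will use a complete case analysis approach, given the pilot nature and short follow-up period". The primary end point is not exempted.

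The section goes on to say that the reepithelialization rate will be set against published historical controls, on an exploratory basis, to help size future randomized trials. The limitations in the Discussion repeat that the data are needed for that sizing.

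For observation around day 14, Postsurgical Treatment has the site uncovered between days 6 and 8, and Table 2 schedules healing and photographs at weeks 1 and 2. Ethical Considerations allows withdrawal at any time. The article does not say how a patient is scored who loses the graft, is re-grafted, dies or withdraws before day 14.

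**The concern.** Complete-case analysis of a proportion is safe when the reason for a missing value has nothing to do with the outcome. The two reasons offered, the pilot status and the short follow-up, do not bear on that. A short interval may reduce administrative loss, but it does not make the remaining loss unrelated to graft failure. The Introduction itself notes that traumatic wounds carry more contamination and deeper tissue damage than burns, so a patient who cannot be assessed at day 14 because the graft has failed is a realistic possibility.

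Each such patient is a treatment failure who disappears from the denominator, and the error then runs in one direction only. With a target of 10, one patient is worth several percentage points. A flattering rate would make the historical comparison look better than it is and could lead to a later randomized trial that is too small.

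**Working it through.** **Inputs from the article**
- Target size: "we aim to enroll 10 patients over 2 years". Its basis is accrual: "approximately 5 per year, we decided to target cases over a period of 2 years". Check: 5 per year × 2 years = 10, which reproduces the stated figure.
- No alpha, power or effect size is given: "a formal power calculation is not feasible for the primary end point". There is no design calculation to test.
- Expected number of missing day-14 values: not stated.

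**Assumed for illustration**
- S = closures among 10 treated, taken as 7 (and 5 as a check).
- m = failures with no day-14 value, taken as 0 to 3.

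**Formulas**
- Complete-case rate = S/(10 − m).
- All-treated rate, with the m failures counted as non-closure = S/10.
- Inflation = S/(10 − m) − S/10 = S·m/[10(10 − m)].

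**Results for S = 7** (exact Clopper-Pearson 95% intervals). The all-treated rate is 7/10 = 70% (35 to 93%) throughout.

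| m | Complete case | 95% CI | Inflation |
|---|---|---|---|
| 0 | 7/10 = 70.0% | 35 to 93% | 0 |
| 1 | 7/9 = 77.8% | 40 to 97% | 7/90 = 7.8 points |
| 2 | 7/8 = 87.5% | 47 to 100% | 14/80 = 17.5 points |
| 3 | 7/7 = 100% | 59 to 100% | 21/70 = 30 points |

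For S = 5 the inflation is 5/90 = 5.6, 10/80 = 12.5 and 15/70 = 21.4 points for m = 1, 2 and 3.

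**Bounds for S = 7, m = 2.** Worst case 7/10 = 70%, best case (7 + 2)/10 = 90%. The complete-case 87.5% lies near the top of that range.

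**Effect on the later trial.** Assume a 50% control rate (not in the article), a two-sided 5% level and 80% power. Comparing two proportions then needs 93 per arm if the RECELL rate is taken as 70%, 46 at 77.8% and 23 at 87.5%. Two unassessed failures out of 10 would cut the planned size to about a quarter (23/93 = 0.25).

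**The case against.** The strongest reply is that complete case excludes patients without a value, not patients whose graft failed. A reader might infer from the rule that failed grafts are dropped as such. The article does not support that. The site is uncovered about a week before the assessment, healing is recorded at weeks 1 and 2, and the window is ±3 days. A lost or infected graft seen then is an observed value below 95% and stays in as a failure. This stands, and it limits the point to failures that are not examined in the window. No dropout or failure rate is given. The Results report no adverse events or protocol deviations among the 4 patients enrolled by April 2025, although 4 patients are too few to settle the matter.

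A reader might also infer that the complete-case rule turns closure after a disallowed treatment (the list includes "full-layer skin grafts, negative pressure wound closure therapy used solely for skin graft fixation") into a success. It does not. Such a patient has an observed value, so the missing-data rule does not touch the case. How these events are scored is a separate question that the full protocol, not shown, may answer.

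Two further replies stand in part. The plan promises to report missing data, so with 10 patients a careful reader could rebuild the all-treated rate. There is also no test, success threshold or go/no-go rule, the historical comparison is labelled exploratory, and the Discussion admits its bias. These lower the severity. They do not justify a headline rate with the wrong denominator, since that rate is meant to be carried into the next trial's sample size.

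Finally, visits missed for unrelated reasons need not push the complete-case rate up, and scoring them as failures pushes the all-treated rate down. That is a fair objection to the remedy, and the sensitivity analysis is there to meet it.

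**Conclusion.** The concern holds in conditional form. The article fixes complete-case analysis for its primary end point, gives reasons that do not make missingness uninformative, and does not provide for a patient unassessed at day 14 because treatment failed. If there are such patients the closure rate is inflated: by 7.8 points for one and 17.5 points for two, assuming 7 closures among 10 treated. If there are none, the two rules agree. S, m and the 50% control rate are assumptions, and the article does not show that unassessed failures will occur.

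This should be fixed before analysis, which the Results schedule for mid-2026. It is not a fatal defect, because the pilot is descriptive and the intervals are wide under either rule.

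**What to change.** Replace the complete-case rule for the primary end point with wording to this effect:
- The denominator is all patients who received the study graft.
- A patient without a day-14 assessment, or re-grafted at the recipient site before it, counts as not achieved. The re-grafting clause is a scoring rule that ties the outcome to the study graft; it does not bear on how patients are treated.
- The complete-case rate, or best- and worst-case bounds, is reported as a sensitivity analysis, with the reason for each missing value.

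The cost is two or three sentences. Healing and concomitant treatments are already recorded at weeks 1 and 2, so little or no extra data is needed beyond the reason for any missed assessment. The downside is that a purely administrative missed visit is scored conservatively; the sensitivity analysis shows by how much. The change concerns the day-14 end point only.
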